###### IEC materials

IEC materials will be developed based on formative findings and include:

Posters.Pictorial brochures/flip charts.Short video messages in the local languages (Sindhi, Pashto and Urdu).

Materials will be distributed during CG meetings and follow-ups, while videos will be shared via WhatsApp using disappearing message settings to minimise re-distribution and possible contamination.

###### Training

CGs will be trained on heat prevention messaging, use of temperature monitoring devices and data loggers, and community-based surveillance of heat-related illness. They will also be trained to communicate structural intervention decisions effectively.

###### Sessions

Sessions will be led by CGs and conducted separately for men and women, including initial triggering meetings and follow-up sessions supervised by research staff.

Summer (April to June):Fortnightly community meetings.Weekly WhatsApp video messages.Weekly weather alerts.Late summer (July to October)Monthly community meetings.Weekly WhatsApp video messages.Weekly weather alerts.Winter (November to March):Community meetings every other month.No WhatsApp video messages.

### Structural modification

This component will include modifications to existing structures. The structural interventions considered for each household and the communal interventions will comprise the possible options as described in figure 3. The household level interventions are targeted to reduce indoor temperature, and the community interventions will play a role in reducing the effects of high heat for outdoor workers and the community as a whole. The interventions are divided into three categories, heat protection, heat modulation and heat dissipation^27^ (figure 3). Each suggested intervention will be evaluated on site and homeowners will be informed and their consent will be obtained. All interventions will be delivered proportionately in each cluster, that is, equal number of each intervention type in every cluster. Interventions will be decided based on building materials, strength and efficiency, overshadowing, ventilation conditions and consent of residents. Apart from this, all interventions will be assessed for safety in terms of structural safety and resident safety (figure 4). Structural modifications will be documented through building assessments and implementation records and experts, architects and structural engineers will be hired to maintain real time monitoring and evaluation.

**Figure 3 F3:**
[figure not shown]
Categorisation of structural interventions.

**Figure 4 F4:**
[figure not shown]
Building survey and intervention process.

These interventions will be delivered based on a community participatory approach where the community and project will share the cost of intervention to improve ownership as shown in a previous trial.^28^ The community contribution will be at least 30% of the total cost at cluster level and this contribution can be monetary or non-monetary, for example, provision of labour or supplies and individual households will not be excluded solely because of inability to contribute financially.

### Control arm

The control arm will receive routine care and usual public-sector health services and general government or media heat-related information which is available to the wider population with no additional intervention. Selected community representatives will conduct surveillance for heat-related illnesses.

### Data collection

Data collectors will undergo 1 week of training on data collection tools, protocols, device handling and procedures. Competency will be assessed through field-based practice questionnaires.

### Line listing

A household census will be conducted across 85 villages in Matiari to assess eligibility and willingness of the community. Data collected will include household ID, number of stories, household size, presence of elderly, children and women of reproductive age, duration of residence and primary floor and roof materials. Villages will then be reassessed for feasibility, including community cooperation and structural suitability for retrofitting. Based on this, 60 clusters will be shortlisted and 22 clusters will be randomly selected and allocated in a 1:1 ratio to the intervention and control arms.

### Cluster randomisation

We will employ a constrained randomisation procedure as described by Morgan and Rubin,^29^ rather than relying on a single random allocation, the randomisation process will be implemented using the Stata ‘randomise’ command, which generates multiple allocation schemes in the background and evaluates balance across prespecified baseline covariates. An allocation achieving an acceptable level of balance between study arms at the cluster level will then be selected for the trial.

Clusters will be randomly assigned by an independent statistician to the intervention (ReHAB) or control arm. Allocations will be assessed for balance on population density, structural type (single vs double story) and roof type (permanent, semipermanent, natural). To minimise contamination, only non-adjacent villages will be selected as clusters, with a minimum separation distance of approximately 1–2 km.

For in-depth assessments, eight households per arm will be selected using simple random sampling and one adult will be selected from each household using the Kish grid. If the selected individual refuses, another eligible adult will be approached; if all adults of a particular household refuse, the household will be replaced with the next in sequence. Male and female participants will be selected systematically.

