### Sample size

Sample sizes were calculated for both the primary outcomes to provide at least 80% power at the 5% significance level. Based on heat-related symptoms and illness prevalence of 28.9%^21^ and an estimated intracluster correlation coefficient (ICC) of 0.0122, we calculate that 11 clusters per arm (22 clusters in total) with 70 to 80 households per cluster are needed to detect a 30% relative difference in heat-related illnesses while allowing for a 10% attrition rate. We treat 28.9% as a conservative estimate given the longitudinal nature of the primary outcome, as cumulative prevalence over the surveillance period is expected to exceed this single-time point prevalence. To assess quality of life changes, we estimate that with 11 clusters per arm 60 households per cluster are required based on the variability in baseline WHO Quality of Life Brief tool (WHOQOL-BREF) scores reported in Lodhi *et al*,^22^ which documented an average score of 68 (18.0) to detect a difference of 4 points in quality of life score assuming an ICC of 0.015. As the heat-related illness outcome required the larger sample size, the final enrolment target was set at 70–80 households per cluster, which also provides adequate power for the quality-of-life outcome. To assess physiological heat strain, we calculated that a subsample of eight adults (aged 18 years to 60 years) per cluster (balanced by gender) would be required to detect a 15% change in average heart rate, among those who are exposed to heat stress assuming a baseline of 66±12 bpm,^23^ an ICC of 0.1736 and 90% power. Given the complexity of the assessment process, we anticipate a higher attrition rate in this subset and have inflated the sample size by 30% to 10 individuals.

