† Maximum Volume of Oxygen.

‡ Cold and Heat Evaluation Questionnaire.

UTCI, Universal Thermal Climate Index.

Individual heat exposure will be measured among a subset of participants (eight per cluster) using thermochron ibuttons or TempU devices attached to clothing. Participants will be instructed to always wear the device and to place it beside their bed while sleeping.

Participants in the subset will also be provided with Fitbit Inspire 3 devices to capture physiological parameters, including heart rate, body temperature variation, sleep, energy expenditure and physical activity. These devices will be synchronised weekly with the AKU server, charged and returned to participants.

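### The selection rule for the wearable subset draws eight households per arm (16 adults), whereas the sample size needs eight per cluster and plans ten; taken literally, power falls from the stated 90% to about 34–38%.

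*Protocol article*

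**What the plan says.** The protocol article gives the size of the physiological and heat-exposure subset in three places.

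- **Sample size.** The heart-rate calculation concludes that "a subsample of eight adults (aged 18 years to 60 years) per cluster (balanced by gender) would be required". Its inputs are to "detect a 15% change in average heart rate", "assuming a baseline of 66±12 bpm,^23^ an ICC of 0.1736 and 90% power". For attrition, the authors "have inflated the sample size by 30% to 10 individuals". The unit for ten is not repeated, but from the context it is per cluster.
- **Cluster randomisation.** The selection procedure reads: "For in-depth assessments, eight households per arm will be selected using simple random sampling", with one adult taken per household by a Kish grid, and replacement rules for refusals.
- **Data collection from subset population.** "Individual heat exposure will be measured among a subset of participants (eight per cluster"), with the same people receiving the Fitbit devices.

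The Population section says only that a subset of adults is randomly selected, so Cluster randomisation is the sole source of the sampling rule.

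**The concern.** With 11 clusters per arm, the three statements imply 220, 176 and 16 adults. The smallest comes from the instruction that field staff would follow. Eight households drawn at random across an arm of 11 villages must leave at least three villages without a participant, so between-village variation would be barely estimable.

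Every wearable outcome in Tables 1 and 3 comes from this subset: heart rate, sleep, activity, energy expenditure and personal heat exposure. So does thermal comfort. Physiological effects are also a stated secondary objective. At 16 adults, neither the 90% power statement nor the multilevel models planned for these outcomes could be supported.

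**Working it through.** **Inputs from the Sample size section.** Baseline mean 66 bpm, SD 12, change of 15%, ICC 0.1736, 11 clusters per arm, 90% power. Two-sided 5% is assumed, because the section gives its level ("at least 80% power at the 5% significance level") for the primary outcomes only.

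**Difference to detect.** 0.15 × 66 = 9.9 bpm.

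**Which SD is 12?** The same section defines the ICC for continuous outcomes as between-cluster over total variance. Since 25/144 = 0.1736 and 144 = 12², 12 is the total SD.

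**Totals implied**

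| Source | Unit | Per arm | Trial |
|---|---|---|---|
| Sample size, after inflation | 10 per cluster | 110 | 220 |
| Data collection from subset | 8 per cluster | 88 | 176 |
| Cluster randomisation | 8 per arm | 8 | 16 |

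**Step 1: the plan's own figure, eight per cluster.**
- Design effect: 1 + (8 − 1) × 0.1736 = 2.215
- Effective n per arm: 88 / 2.215 = 39.7
- SE of the difference: 12 × √(2/39.7) = 2.69 bpm
- 9.9 / 2.69 = 3.68
- Power: 95.7% (normal) or 93.8% (t, 20 df)

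The stated 90% is met with some margin.

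**Step 2: the selection rule as written, eight per arm.** Treating the adults as independent, which favours the plan:
- SE: 12 × √(2/8) = 6.0 bpm
- 9.9 / 6.0 = 1.65
- Power: 37.8% (normal) or 33.7% (t, 14 df)

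With villages of similar size, two adults share a village with chance 1/11, so the average design effect is 1 + 7 × 0.1736/11 = 1.11. Power is then 34.7% (normal) or 30.9% (t).

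With 30% loss, 8 × 0.7 = 5.6 adults per arm remain. The SE is 12 × √(2/5.6) = 7.17 bpm and power is about 28% (normal) or 24% (t).

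The difference detectable with 90% power is 6.0 × (1.960 + 1.282) = 19.4 bpm (29% of baseline) on the normal approximation, or about 21 bpm (32%) on the t distribution.

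**Step 3: eight versus ten per cluster.**

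| Adults per cluster analysed | Design effect | SE (bpm) | Power, normal | Power, t (20 df) |
|---|---|---|---|---|
| 10 | 2.562 | 2.59 | 96.9% | 95.3% |
| 8 | 2.215 | 2.69 | 95.7% | 93.8% |
| 7 (ten less 30%) | 2.042 | 2.76 | 94.8% | 92.6% |
| 5.6 (eight less 30%) | 1.799 | 2.90 | 92.7% | 90.1% |

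The choice between eight and ten moves power by a few points at most. The choice between per arm and per cluster is an eleven-fold difference in sample size and moves power by nearly 60 points.

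**The case against.** The strongest reply is that one word is wrong. The Sample size section and the device section both count by cluster, the calculation uses an ICC that would have little purpose if eight people were drawn per arm, and the analysis models clustering. On that reading, 34–38% is what would follow from literal execution and not the trial's likely power. This is fair, and "per arm" probably is a slip. But a sampling rule has to be executable as written, and this is the only one the article gives.

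Further points on the other side:

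- Eight and ten within the Sample size section do not conflict: one is the number required, the other the number after the allowance. This stands. What remains is that the device section carries the uninflated number, and Step 3 shows that this matters little.
- Eight random households would reach about 11 × (1 − (10/11)⁸) = 5.9 villages on average, so some villages would contribute two adults. This stands too: village variance would be very poorly estimated, but not strictly inestimable.
- If 12 were the within-cluster SD, seven per cluster would give 90.3% (normal) or 87.2% (t), so ten enrolled might fall just short. The protocol's own ICC definition, with 0.1736 = 25/144, rules that reading out.
- The power figures ignore the repeated heart-rate records. So does the protocol's own calculation, and the comparison here is like for like.
- Neither co-primary outcome is touched. This is true and limits the reach of the point, but not the need to correct it.

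**Conclusion.** The concern holds. The operative selection rule gives 16 adults where the sample size requires 176 and plans 220, and nothing in the article reconciles them. Followed literally, it yields about 34–38% power for the 15% heart-rate change, or 31–35% allowing for chance selection from the same village, against a stated 90% that eight per cluster does meet (94–96%).

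These figures assume two-sided 5% testing, 12 as the total SD, one heart-rate value per person, and no loss except where shown. The conflict that matters is per arm versus per cluster; the eight-versus-ten mismatch is minor. The consequences are confined to the subset outcomes. Because the number in question is the sample size behind a stated power, it must be corrected even if its origin is a slip.

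**What to change.** - **Cluster randomisation:** state that ten households per cluster are selected by simple random sampling within each village, with one adult per household and gender balanced within the village (110 adults per arm, 220 in total).
- **Data collection from subset population:** change eight per cluster to ten per cluster.
- **Sample size:** add "per cluster" after the inflated figure, and say that ten enrolled with 30% loss leaves seven, which gives about 93–95% power. This wording is needed because inflating eight for a 30% loss would strictly give 8/0.7 = 11.4. Ten is adequate because seven per cluster already exceeds 90%, not because it preserves eight.

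If the subset has already been drawn, report the number actually enrolled per village. The cost is wording only, since ten per cluster is the enrolment that the Sample size section already plans.

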### Household data collection

Baseline, periodic (monthly/weekly) and endline surveys (Table 3) will be conducted in all the 22 intervention and control clusters. Data will be collected on demographics (household size, socioeconomic status, education, occupation, ethnicity), healthcare-seeking behaviour, mental health (WHO well-being scale), food security, dietary diversity, comorbidities, medications and symptoms of heat-related illness (box 1).

Box 1Section for data collection toolDescription of modules and their sectionsModule-A: Household identification and demographic informationSection-A1: Household identification and consentSection-A2: Household members’ informationSection-A3: Socioeconomic status of householdSection-A4: Building surveySection-A5: Household water and sanitation statusModule-B: Household food insecurity, dietary diversity and source assessmentSection-B1: Household Food Insecurity Experience ScaleSection-B2: Household Dietary Diversity and Source AssessmentModule-C: Health and hygiene assessment of adult participantsSection-C1: General health and disabilitiesSection-C2: Mental healthSection-C3: Hygiene practices (hand washing, dental hygiene, bath (menstrual hygiene for females))Module-D: Heat exposure/sleep/dietary assessmentSection D1: Work and sun exposureSection D2: At-home heat exposureSection D3: Heat stress experiences, food security and adaptation strategiesSection D4: Knowledge about heat-related health problems, existing heat adaptation and prevention strategiesSection-D5: SleepSection-D6: Quality of life

The questionnaire was adapted from validated tools used in similar settings, with modifications for local relevance. It was translated into the local language and back translated into English to ensure accuracy.

Data on signs and symptoms of heat-related illness will be collected through multiple sources to minimise missed events during the study period in the intervention and control clusters. Suspected heat-related illness episodes identified through community surveillance, household surveys or health facility records will be classified according to the predefined symptom-based algorithm by study data collectors as presented in figure 2 and categorised using International Classification of Disease, 11th Revision and institutional criteria. Events that would be identified through community surveillance will be visited by data collectors who will use the same survey tool, and reported health facility visits will be verified through facility records, where feasible. Quality of life data will be obtained through repeated household surveys, with the selected index adult serving as the respondent (Table 3).

Quantitative data will be collected using handheld devices with a custom-built Java application, with MySQL and SQLite used for data storage. Built-in range checks, consistency checks and skip patterns will minimise data entry errors. Any discrepancies will be verified and resolved through follow-up with data collectors. Each participant will be assigned a unique identifier generated by the purpose-built Android application to maintain anonymity. All data will be securely stored behind firewalls and fully anonymised prior to analysis.

In the second year of intervention, 5 mL venous blood samples will be collected from participants in both intervention and control households during peak heat time. Samples will be obtained by trained phlebotomists using standard aseptic techniques and stored in a biobank according to established protocols. These samples may be used for future exploratory analysis of heat-related biomarkers which have not been specified yet.

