### Study design

This study is a 2-year prospective, cluster-randomised controlled trial designed to evaluate the effectiveness of ReHAB intervention in rural settings. One village will serve as one cluster with 70–80 households randomized, and these clusters will be randomly assigned to either the intervention or control arm in a 1:1 ratio (figure 1). Due to the nature of the intervention, blinding of participants and researchers will not be feasible, but data analysis would be blinded. The trial is registered on clinicaltrial.gov with trial registration number NCT06983483. The study field activities will run from 1 January 2026 to 31 December 2027.

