### Outcomes

All primary, secondary and outcomes assessed for subset of population along with definitions are provided in table 1 and figure 2.

**Table 1 T1:** Outcomes

Primary outcomes	
Heat-related illness	Defined as a documented heat condition/illness according to the International Classification of Disease-11th Revision and institutional classification which classifies heat-related illness as heat stroke, heat syncope, heat exhaustion, heat fatigue, heat cramps and heat rash (figure 2).^30 31^
Quality of life	Quality of life would be assessed according to the WHOQOL-BREF* tool and assessed during two consecutive peak summer and winter seasons.

Secondary outcomes	
Health outcomes	
All-cause mortality	Defined as the total number of deaths in the study population over the study period
Hospital visit/hospitalisation	Defined as the number of hospital admissions (primary, secondary or tertiary facilities) during summers
Environmental outcomes	
Heat Index	Indoor heat index (temperature and humidity)^32^ measured through fixed weather devices
Universal Thermal Climate Index	Defined as a biometeorological index that describes the human body’s physiological response to the environment. It integrates air temperature, humidity, wind speed and radiant temperature to assess the overall thermal stress on the human body
Thermal comfort	Defined as change in the condition of mind that expresses satisfaction with the thermal environment
Outcomes measured for subset of population (individual level)	
Personalised heat exposure	Defined as mean daily external temperature each individual experiences (indoors and outdoors) as recorded by a wearable temperature monitor.
Heart rate	Defined as mean heart rate measurements (beats per minute) taken at 1-hour interval as recorded by wearable android device
Sleep quality	Defined as a biological process that alternates between non-rapid eye movement sleep and rapid eye movement sleep as recorded through a wearable android device
Physical activity	Defined as mean daily duration of sedentary, lightly active, moderately active and very active as measured using a wearable android device.
Energy expenditure	Defined as average total number of calories burned in a day recorded using a wearable android device.
Economic outcomes	
Cost-effectiveness	Measured as the difference in cost divided by the difference in health effect between the intervention and control groups

* WHO Quality of Life Brief tool.

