##### Community education and awareness

The educational component of ReHAB was developed based on findings from the formative phase, including systematic review, qualitative work, stakeholder consultations and pilot testing. Community mobilisation will be implemented throughout the intervention. Community groups (CGs) will be established across all 11 intervention clusters, with separate male and female representation. Each CG (6–8 members) will include local government representatives, elders, religious leaders and male and female community members. CGs will lead mobilisation activities and support surveillance of the primary outcome (heat illness).

Activities will include dissemination of heatwave warnings, awareness sessions and door-to-door outreach on heat-health practices (hydration, clothing and activity scheduling). CGs will maintain logbooks to record healthcare visits within their catchment areas and attendance in community meetings. Practical demonstrations of cooling strategies (eg, shade setup, light clothing, wet towels, misting and work–rest–shade cycles) will be conducted, supported by Information, Education and Communication (IEC) materials. This structured, behaviour-focused delivery aims to ensure both the uptake and sustainability of protective cooling practices. Community hydration measures (eg, temporary drinking water facilities) will also be implemented to reduce dehydration among outdoor workers.

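### Whether a suspected episode counts as heat-related illness is decided by data collectors who are in effect unblinded, although the predefined rule could be run on the stored symptoms without arm labels

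*Protocol article*

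**What the plan says.** All references are to the protocol article.

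- **Who classifies.** Household data collection states that suspected episodes from community surveillance, household surveys or facility records "will be classified according to the predefined symptom-based algorithm by study data collectors as presented in figure 2".
- **How collectors meet cases.** The same section says "Events that would be identified through community surveillance will be visited by data collectors who will use the same survey tool".
- **How answers are stored.** The same section says "Quantitative data will be collected using handheld devices with a custom-built Java application", with a database behind it.
- **External check.** The only one described is that "reported health facility visits will be verified through facility records, where feasible".
- **Blinding.** Study design states that "blinding of participants and researchers will not be feasible, but data analysis would be blinded".
- **Use of the classification.** Primary outcome analysis divides the number of episodes by person-weeks at risk in a Poisson model with cluster random intercepts. A new episode starts after at least 2 symptom-free days, or when new symptoms are added to an ongoing illness.
- **Testing order.** Sample size tests heat-related illness first at two-sided 0.05, and quality of life only if that test is significant.

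The article describes no arm-masked classification or adjudication.

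**The concern.** The article treats blinding as unattainable for everyone except the analyst. That is reasonable for residents and field staff in a trial of roofs, walls, shading and shelters. It does not follow for the step that turns recorded symptoms into a counted event. That step applies a predefined, symptom-based rule to answers already captured electronically, and it needs no knowledge of the village.

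As written, the rule is applied by the people most exposed to the allocation. If knowing the arm shifts their yes/no decision, or their reading of whether added symptoms start a new episode, the shift is built into the numerator before the analyst sees any data. Because the first test gates the second, a distorted count could wrongly open or wrongly close the route to the quality-of-life conclusion.

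**Working it through.** **Step 1. Do the collectors know the arm?** No sentence says so. It follows from two statements together: researchers are not blinded, and collectors go in person to cases in villages where the structural work is visible. This is an inference, though a secure one.

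**Step 2. Which decisions enter the count?** Primary outcome analysis counts episodes whatever their type. Two decisions therefore matter: whether an episode is a heat-related illness, and whether it is new.

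**Step 3. Can the rule be run without the arm?** The rule is predefined and symptom-based, the answers are electronic, and the new-episode rule uses dates and symptoms. De-duplication is already done on database fields that include onset date, symptoms and care-seeking. Running the rule on a file without cluster and arm identifiers is therefore feasible, apart from cases the algorithm leaves unclear. Figure 2 is not shown, so their number is unknown.

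**Step 4. The plan's own figure.** Inputs from Sample size: 28.9% in control, a 30% relative difference (0.289 × 0.70 = 0.2023), ICC 0.0122, 80% power, 5% level, 70 households per cluster less 10% = 63.
- Individually randomised n per arm: 386.
- Design effect: 1 + (63 − 1) × 0.0122 = 1.756.
- Clusters per arm: 386 × 1.756 / 63 = 10.76, rounded up to 11.

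The stated 11 clusters per arm is reproduced, and no stated figure is in dispute.

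**Step 5. Illustration of a shift in the rate ratio.** The documents give no misclassification rate. Assume that a share d of true episodes is additionally rejected in one arm.
- Extra rejection in the intervention arm: observed IRR = true IRR × (1 − d).
- Extra rejection in the control arm: observed IRR = true IRR / (1 − d).

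| d (assumed) | True 1.00, intervention arm | True 1.00, control arm | True 0.70, intervention arm | True 0.70, control arm |
|---|---|---|---|---|
| 5% | 0.95 | 1.05 | 0.67 | 0.74 |
| 10% | 0.90 | 1.11 | 0.63 | 0.78 |
| 15% | 0.85 | 1.18 | 0.60 | 0.82 |

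**Step 6. What that does to the test.** This uses a simple two-proportion comparison with the planning inputs, not the planned Poisson model, so it is an order of magnitude only. The effective n per arm is 11 × 63 / 1.756 = 394.6.

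Take no true effect and d = 10% in the intervention arm:
- Observed proportions: 0.289 and 0.2601, difference 0.0289.
- SE = √[(0.289 × 0.711 + 0.2601 × 0.7399) / 394.6] = 0.0318.
- Ratio: 0.0289 / 0.0318 = 0.91.
- Rejection probability: 1 − Φ(1.96 − 0.91) + Φ(−1.96 − 0.91) = 0.149.

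The same formula gives 0.074 at d = 5% and 0.281 at d = 15%, against a nominal 0.05. If the extra rejection is in the control arm, the probabilities are the same, but the spurious result mostly points against the intervention.

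Take a true ratio of 0.70 and d = 10% in the control arm:
- Difference: 0.2601 − 0.2023 = 0.0578.
- SE = √[(0.2601 × 0.7399 + 0.2023 × 0.7977) / 394.6] = 0.0299.
- Power: Φ(0.0578 / 0.0299 − 1.96) ≈ 0.49, against 0.81 when d = 0.

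**The case against.** The strongest reply is that the argument cuts against itself. If the algorithm is mechanical enough to be programmed, a collector applying it has little discretion and central derivation gains little. If it needs field judgement, a program cannot replace it. In either case much of the risk lies in how symptoms are asked about and reported, and that stays with unblinded collectors and participants. An article may also omit that the application already computes the class.

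Most of this stands as a limit on the size of the gain. It does not remove the point: a mechanical rule also makes masked derivation trivial, and the text as published assigns the decision to collectors.

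A reader might infer more than the documents support:
- **That misjudging the type of illness biases the co-primary.** The type does not enter the count.
- **That mild categories turn on a judgement about whether heat was the cause.** No visible text says so, and Figure 2 is not shown.
- **That Table 1 contradicts the field procedure by requiring a documented condition.** The wording is "Defined as a documented heat condition/illness according to the International Classification of Disease-11th Revision and institutional classification", and the same row refers to Figure 2, the algorithm the collectors use. An episode recorded with the survey tool can count as documented.
- **That facility-verified episodes would give a cleaner answer.** Verification depends on care-seeking, which an education programme may itself change, and on records being obtainable.
- **That the bias must favour the intervention.** In intervention villages, the community groups that lead mobilisation also support surveillance. In control villages, "Selected community representatives will conduct surveillance for heat-related illnesses". Greater awareness could raise intervention-arm counts.

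**Conclusion.** The point holds for the yes/no and new-episode decisions. The protocol assigns an outcome-defining step to staff who can be taken to know the arm, and blinded analysis cannot correct it afterwards. The step is avoidable, feeds the first co-primary directly and affects the second through the testing sequence, so it should be changed.

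The size and direction of the bias are unknown. The 5% to 15% range is assumed. Over that range the rate ratio moves by about the same proportion, in either direction. In the simplified calculation, the chance of a significant result with no true effect rises from 0.05 to between 0.07 and 0.28. These figures rest on the planning proportions, 63 retained households per cluster and a two-proportion test. They show what a differential of that size would do, not that one exists.

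Two uncertainties remain. The collectors' knowledge of the arm is inferred, and the discretion left by Figure 2 cannot be checked.

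**What to change.** Amend Household data collection as follows:

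1. Collectors record signs, symptoms, onset and end dates and care-seeking only. They no longer make the decision that enters the primary analysis.
2. A program, locked before the analysis, derives heat-illness status (yes/no) under Figure 2 and applies the new-episode rule from Primary outcome analysis. It runs on stored data with cluster and arm identifiers removed.
3. The field classification is retained as a sensitivity analysis, and agreement between the two is reported by arm.
4. Unblinded symptom elicitation, self-report and the different case finders in the two arms are stated as remaining limitations.

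The cost is a coded rule in the existing application or database, a step to strip identifiers, and a wording amendment. No visits are added and the sample size stays at 11 clusters per arm. The drawback is that some field context is lost for episodes the algorithm does not settle. The field-classification sensitivity analysis shows how much that matters.
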